#### Dropout exclusion criteria

2.3.3

Patients who discontinue treatment due to any of the following reasons (including but not limited to) will be a dropout case: (1) voluntary withdrawal by participants for any personal reasons; (2) the patient’s symptoms do not improve and gradually worsened after treatment; (3) patients are unreachable due to relocated or changed contact information; (4) patients undergo changes in health status that need a timely manner; (5) patients experience intolerable side effects and are unwilling to continue treatment.

#### Exit/termination criteria

2.3.4

The exit/termination criteria are as follows: (1) patients do not meet the inclusion criteria and are enrolled mistakenly; (2) patients receive other or additional FD treatments during the study period.

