#### Strategies to improve adherence to interventions

2.3.5

In order to mitigate the impact of dropout rates on research quality, we will enhance participant compliance through several strategies: (1) researchers will regularly contact with participants via WeChat or phone calls to understand their condition and remind them about the schedule of their next visit; (2) we will schedule treatment and evaluation sessions at convenient times to minimize the disruption to participants’ work and daily lives; (3) the evaluation process will be simplified to enhance patient engagement; (4) participants will be reimbursed for treatment expenses and transportation costs to and from the hospital; (5) dedicated staff will be available to address any study-related inquiries raised by participants.

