### Intervention

2.6

This trial consists of a screening phase (1 week), a treatment phase (4 weeks), and a post-treatment follow-up phase (12 weeks). During the treatment period, participants in the verum acupuncture plus placebo group will receive 12 sessions of verum acupuncture treatment and itopride placebo tablets for 20 days. Patients in the itopride plus sham acupuncture group will take itopride tablets for 20 days and receive 12 sessions of sham acupuncture treatment. Patients in the sham acupuncture plus placebo group will take itopride placebo tablets for 20 days and receive 12 sessions of sham acupuncture treatment. The detailed treatment procedures is as follows:

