### Outcome

2.7

Primary outcomes in this study include the proportion of responders (PR) and the elimination rate of the main symptom. The secondary outcomes include changes in symptom score, QOL, mood during the treatment and follow-up, and the participants’ expectancy for acupuncture before treatment, as well as related hormone concentrations. Table 2 display a summary of all measurements. Follow-up for all participants can be completed via social media (WeChat) or phone.

**Table 2 tab2:** SPIRIT figure for the schedule of enrollment, interventions, and assessments.

	Study period								
	Enrolment	Allocation	Treatment phase				Follow-up		
Timepoint**	*1w*		*2w*	*3w*	*4w*	*5w*	*9w*	*13w*	*17w*
Enrolment									
Eligibility screen	X								
Informed consent	X								
Allocation		X							
Interventions									
Verum acupuncture plus placebo									
Itopride plus sham acupuncture									
Sham acupuncture plus placebo									
Assessments									
Proportion of responders			X	X	X	X	X	X	X
Elimination rate			X	X	X	X	X	X	X
NDSI		X				X	X	X	X
SF-NDLQI		X				X	X	X	X
HADS		X				X	X	X	X
Acupuncture expectation		X							
Related hormone concentrations		X				X			
Adverse events			X	X	X	X			

SPIRIT, standard protocol items: recommendations for interventional trials; NDSI, the nepean dyspepsia symptom index; SF-NDLQI, the short form - Nepean Dyspepsia Life Quality Index; HADS, Hospital Anxiety and Depression Scale.

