#### Primary outcome

2.7.1

**The proportion of responders (PR)** Patients experiencing sufficient alleviation of stomach discomfort are categorized as positive responders (23). Participants will be requested to evaluate changes in their symptom relief over the preceding 7 days via a 7-point Likert scale. This scale features options such as “extremely worsened,” “worsened,” “slightly worsened,” “no change,” “slightly improved,” “improved,” or “extremely improved,” which correspond to scores ranging from 0 to 6. Those participants who report a relief score of either 5 or 6 points will be deemed positive responders. The measurement of PR will take place at weeks 2, 3, 4, 5, 9, 13, and 17.

**The elimination rate (ER)** ER refers to the proportion of patients whose main symptoms have disappeared. According to Rome IV criteria, we define postprandial fullness and bloating as the main symptoms. Included patients should have at least one of these symptoms. Using a 7-point Likert scale, the main symptoms are considered to have disappeared if the rating drops to 0 after treatment. ER will be measured at weeks 2, 3, 4, 5, 9, 13, and 17.

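### Sections 2.3.3 and 2.3.4 do not say that patients who stop treatment or take other dyspepsia therapy are still rated, so follow-up outcomes may be lost for outcome-related reasons

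*Protocol article*

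**What the plan says.** Section 2.3.4 (Exit/termination criteria) has two entries. The second is that "patients receive other or additional FD treatments during the study period". Section 2.6 sets 4 weeks of treatment and then 12 weeks of follow-up, so the criterion can apply long after study treatment has ended.

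Section 2.3.3 (Dropout exclusion criteria) states: "Patients who discontinue treatment due to any of the following reasons (including but not limited to) will be a dropout case". One listed reason is that the patient's "symptoms do not improve and gradually worsened after treatment"; another is intolerable side effects. The same list contains voluntary withdrawal and patients who cannot be reached.

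On outcomes, section 2.7.1 states: "The measurement of PR will take place at weeks 2, 3, 4, 5, 9, 13, and 17". The elimination rate (ER) has the same schedule as the proportion of responders (PR). Section 2.7 adds: "Follow-up for all participants can be completed via social media (WeChat) or phone". Section 2.12 analyses all randomised patients by assigned group, whether or not they completed as planned, and imputes missing primary outcomes by multiple imputation under a missing-at-random assumption. Sensitivity analysis is left to be done if needed.

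**The concern.** Stopping study treatment, starting another therapy and leaving the study are three different events. Sections 2.3.3 and 2.3.4 do not separate them. A site that follows the text could reasonably stop rating a patient who relapses and takes a prokinetic in follow-up, because that patient has met an exit criterion. Three hospitals could also apply the wording differently.

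Patients who leave because they worsened or needed rescue are those for whom missing at random is least credible. Follow-up ratings are 4 weeks apart and PR looks back only 7 days. If rating stops at exit, a relapse that begins after week 5 and is treated before week 9 may never appear in the data. No later analysis plan can recover ratings that were not taken. The promise in section 2.12 to analyse everyone by assigned group is best served by outcomes observed after stopping.

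**Working it through.** **1. The plan's own figure.** Section 2.11 gives responder rates of 70.69% (acupuncture) and 55.46% (itopride), a margin of 10 points, one-sided alpha 0.025 and 80% power.

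n = (1.960 + 0.842)² × (0.7069 × 0.2931 + 0.5546 × 0.4454) / (0.1523 + 0.10)² = 7.849 × 0.4542 / 0.06366 = 56.01, rounded up to **57**. This agrees with the article. With 15% dropout, 57 / 0.85 = 67.06, and the article uses 67. The allowance is therefore 67 − 57 = 10 per arm, or 30 of 201. It is not split by reason or time, and it includes unreachable patients whom no wording would recover.

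**2. Which rule acts when.**

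| Period | Rule that can apply | PR/ER ratings |
|---|---|---|
| Treatment, weeks 2–5 | 2.3.3 (stopping treatment) and 2.3.4 (other therapy) | 2, 3, 4, 5 |
| Follow-up, weeks 6–17 | 2.3.4 only, for new exits | 9, 13, 17 |

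Section 2.3.3 depends on stopping treatment, which lasts 4 weeks. A new exit in follow-up therefore rests on the second entry of 2.3.4 alone. Follow-up is 12 / (4 + 12) = 75% of the time after allocation. It holds 3 of 7 PR/ER ratings and 3 of 4 post-baseline assessments of the dyspepsia symptom index, the quality-of-life index and the anxiety and depression scale.

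**3. Does any other section require rating after exit?**
- Section 2.7 gives the mode of contact for all participants. It does not say that an exited patient is still one.
- Section 2.12 fixes who is analysed, not who is observed.
- Section 2.3.5 mentions evaluation sessions in a list of adherence measures, without reference to patients who stopped.

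All three are compatible with continued rating. None requires it.

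**4. Size, under assumed inputs.** Suppose k unrated patients in one arm of 67 truly respond d points less often than imputed. That arm's PR is overstated by k/67 × d:
- k = 3, d = 20: 0.9 points
- k = 5, d = 20: 1.5 points
- k = 10, d = 20: 3.0 points
- k = 10, d = 50: 7.5 points (extreme: the whole allowance in that arm)

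These are one-arm figures. The same k and d in both arms leave the difference unchanged.

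**5. Effect on a non-inferiority conclusion, under extreme assumptions.** Take a true difference of exactly −10 points (itopride 55.46%, acupuncture 45.46%), all unrated patients non-responders, and imputation with no useful earlier data. Each arm's estimate is then p / (1 − exit fraction). For exits of 15% acupuncture and 5% itopride: 0.4546/0.85 − 0.5546/0.95 = 0.535 − 0.584 = −4.9 points.

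| Exits, acupuncture / itopride | Estimated difference | Chance of declaring non-inferiority (nominal 2.5%) |
|---|---|---|
| 15% / 15% | −11.8 | 1.6% |
| 15% / 5% | −4.9 | 8.1% |
| 15% / 0% | −2.0 | 14.3% |
| 5% / 15% | −17.4 | 0.3% |

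Even with equal exit fractions the estimate moves slightly, because the imputed rates, and so d, differ between arms: 0.15 × (65.2 − 53.5) = 1.8 points. The error can go either way, and imbalance between arms drives it.

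**The case against.** The strongest objection is that the end of rating is inferred. Neither section says what happens to later ratings, the article condenses a fuller protocol, and visit procedures after discontinuation are often set out there. This stands as a limit on the claim. A reader might infer that the protocol orders outcome collection to stop; the article does not say that. It does, however, state the exit rule itself, and that rule is worded so that following it can lose outcomes.

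Two pieces of apparent support are weak. Section 2.3.5 opens with "In order to mitigate the impact of dropout rates on research quality", but under a heading about adherence to interventions, so dropout there may mean only stopping treatment. The 15% allowance would be needed for unreachable patients and withdrawals alone. Neither shows that treatment stoppers or rescued patients go unrated.

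The powered comparison is also little exposed. Section 2.11 sizes the trial on response at the end of 4 weeks, and weekly ratings before that point carry information into the imputation. The assumption of no useful earlier data in step 5 therefore overstates the problem at week 5.

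A reader might also set 7.5 points against the 10-point margin, or take 14.3% as the trial's error rate. Neither is supported: the first is an extreme one-arm figure and the margin concerns a difference between arms, while the second assumes a 15% versus 0% imbalance that nothing in the article suggests.

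Finally, the choice of primary handling for rescue belongs in the analysis plan, and ratings after rescue can pull the arms together. Both are true, but neither is a reason to leave the ratings uncollected.

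**Conclusion.** The concern holds in a limited form. The article makes other dyspepsia treatment at any time in the study an exit criterion and groups treatment stoppers with patients lost to contact. It nowhere says that either group is still rated. On the natural reading of exit, PR and ER at weeks 9, 13 and 17 are the outcomes mainly exposed, through section 2.3.4. The end-of-treatment non-inferiority comparison is exposed only through stopping or rescue in weeks 2 to 5, and less so because of the weekly ratings.

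Neither the size nor the direction of bias can be derived from the document. The illustrations rest on assumed numbers of unrated patients and assumed departures from the imputed rates, and the comparison is biased only where those departures differ between arms. This is a cheap improvement worth making early, since missed ratings cannot be collected later. It is not evidence that the main comparison is invalid.

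**What to change.** Amend sections 2.3.3 and 2.3.4 to state:
- Stopping study treatment or starting other dyspepsia therapy ends study treatment only. In follow-up, where no study treatment remains, it changes nothing in the visit schedule.
- The patient stays in the study and gives all remaining scheduled questionnaires by WeChat or phone, unless consent for contact is withdrawn or the patient cannot be reached.
- The date and reason for stopping, and the name and start date of any other dyspepsia therapy, are recorded.

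Add a sensitivity analysis of PR and ER that counts ratings after other dyspepsia therapy as non-response. Leave the primary handling to the sponsor, to be fixed before unblinding. Clinical decisions to stop treatment stay as they are.

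**Cost.** Protocol wording needs ethics approval (section 2.10), plus one case report form page. A patient who stops before the week-2 rating has 7 ratings left, so the upper limit is 30 × 7 = 210 short contacts if all 30 allowed dropouts were reachable. If all 30 left before the week-5 rating, each would have at least 4 left, giving 120 to 210. If all left only after week 13, the figure would be 30. The true number will be lower because some patients are unreachable or withdraw. The secondary questionnaires fall in the same weeks and need no extra contact. The downside is that ratings after rescue carry the rescue effect, which is why the sensitivity analysis is needed.

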#### Strategies to improve adherence to interventions

2.3.5

In order to mitigate the impact of dropout rates on research quality, we will enhance participant compliance through several strategies: (1) researchers will regularly contact with participants via WeChat or phone calls to understand their condition and remind them about the schedule of their next visit; (2) we will schedule treatment and evaluation sessions at convenient times to minimize the disruption to participants’ work and daily lives; (3) the evaluation process will be simplified to enhance patient engagement; (4) participants will be reimbursed for treatment expenses and transportation costs to and from the hospital; (5) dedicated staff will be available to address any study-related inquiries raised by participants.

### Randomization, allocation, and concealment

2.4

A research assistant at each clinical institution will conduct random assignments independently from other study activities. Eligible patients will be randomly assigned into the verum acupuncture plus placebo group, itopride plus sham acupuncture group, and sham acupuncture plus placebo group in a 1:1:1 ratio. A professional statistician will utilize SAS software (v9.3) to produce a list of random numbers stratified by clinical institution using block sizes of 6 or 9. The randomization process will be carried out through an online central randomization system. The randomization number and group assignment provided to each patient by the randomization system will be unique and unchangeable, ensuring fairness in treatment allocation.

### Blinding

2.5

This study will maintain blinding among patients, observers, and statisticians. However, acupuncturists will not be blinded due to the nature of the acupuncture procedure. Patients will be informed that the study involves two types of acupuncture treatment and two types of drug, which theoretically can improve PDS symptoms. Regardless of their assigned group, patients will receive a combination treatment comprising one type of acupuncture treatment and one type of drug. Sham acupuncture will be performed by using Streitberger needles. Itopride placebo tablets will be indistinguishable from verum itopride tablets in taste and appearance. Each patient will undergo treatment in separate rooms to prevent communication between them. Acupuncturists, who will not be blinded, must refrain from discussing assignment information with participants. In the case the trial goes well, the research center will perform unblinding once the statistical analysis is complete. However, if any emergencies arise, such as life-threatening adverse events (AEs), the academic center will perform urgent unblinding. The monitoring team and ethics committee will then analyze the relationship between patient intervention strategies and AEs.

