Notably, acupuncture treatment, a method found in traditional Chinese medicine (TCM), can improve FD symptoms through multiple molecular mechanisms (11). It is currently recognized as a significant complementary and alternative therapy for the management of FD (12). Multiple meta-analyses revealed that acupuncture is more effective than the single use of prokinetic drugs or sham acupuncture in improving digestive symptoms and quality of life in patients with FD (13, 14). Moreover, another system review found that acupuncture combined with Western medicine has a synergistic effect in the treatment of FD while helping to reduce the relapse rate within 3–6 months after treatment (15). Additionally, the evidence has shown that acupuncture can regulate gastrointestinal function by improving gastrointestinal motility and reducing visceral sensitivity, which supports the potential of acupuncture as a therapeutic option for FD (16). However, due to limited high-quality evidence (evidence grade B), a recent consensus statement did not endorse acupuncture for FD, highlighting the need for further high-quality RCTs to clarify its therapeutic potential and role in FD management (8).

Previous clinical trials have compared the therapeutic effects of acupuncture with prokinetic agents in patients with FD, revealing acupuncture as a superior way to prokinetic agents (17, 18). However, these studies were open-lable and lacked blinding, potentially allowing patient preferences for acupuncture to influence clinical outcomes. To obtain more high-quality evidence, we design a new randomized trial; this trial will administer different treatments (acupuncture or the drug itopride) in a double-dummy, single-blind design to objectively evaluate the effectiveness and safety of acupuncture for PDS compared to itopride.

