### Study setting and recruitment

2.2

This clinical trial will be conducted collaboratively by an academic center and three clinical institutions. Researchers from the Hunan University of Chinese Medicine will form an academic center group responsible for experimental design, data analysis and results dissemination. Recruitment, treatment and data collection will occur at the First Affiliated Hospital of Hunan University of Traditional Chinese Medicine, the Second Affiliated Hospital of Hunan University of Traditional Chinese Medicine, and Changsha Hospital of Traditional Chinese Medicine. Recruitment is scheduled to take place at inpatient and outpatient departments in three clinical institutions, and start in December 2024, with the follow-up assessments of all participants completed by December 2027. Recruitment information will be disseminated through various means such as paper flyers, posters, and social platform like Wechat. Participants interested in this trial will be informed about the purpose and process of the study as well as potential risks and benefits. If the patient decides to participate after understanding this information, they will undergo a clinical screening evaluation conducted by registered TCM practitioners with a minimum of 5 years of clinical experience. Eligible patients will sign an informed consent form, receive baseline assessment, and be randomly assigned.

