**Figure 2 fig2:**
[figure not shown]
Stimulation points. ST2, Sibai; ST21, Liangmen; ST36, Zusanli; PC6, Neiguan; SP4, Gongsun.

**Table 1 tab1:** Locations and manipulations of acupoints.

Acupoint	Location	Depth of needle penetration in verum acupuncture treatment
Sibai (ST2)	In the face, directly below the pupil, and in the depression of the infraorbital foramen.	Inserted perpendicularly at 0.5 cun with 0.25 mm*25 mm acupuncture needles.
Liangmen (ST21)	In the abdomen, 4 cun above the umbilicus, and 2 cun lateral to the anterior midline.	Inserted perpendicularly at 0.8–1.2 cun with 0.3 mm*40 mm acupuncture needles.
Neiguan (PC6)	In the flexor aspect of the forearm, between the tendons of palmaris longus and flexor carpi radialis, 2 cun above the transverse crease of the wrist.	Inserted perpendicularly at 0.5–0.8 cun with 0.25 mm*25 mm acupuncture needles.
Zusanli (ST36)	In the anterior aspect of the lower leg, 3 cun directly below Dubi (ST35), and one finger-breadth lateral to the anterior border of the tibia.	Inserted perpendicularly at 1–1.5 cun with 0.30 mm * 50 mm acupuncture needles
Gongsun (SP4)	In the anterior and inferior of the base of the first metatarsal bone, and on the dorso-ventral boundary.	Inserted perpendicularly at 0.5–0.8 cun with 0.25 mm*25 mm acupuncture needles

1 cun is defined as the width of the interphalangeal joint of the patient’s thumb. Dubi (ST35) is in the lateral depression of the patellar ligament when the knee is flexed.

In the sham acupuncture protocol, Streitberger needles will be applied at the same acupoints as those used in the verum acupuncture treatment. The Streitberger needle is a non-penetrating acupuncture placebo device that has been well validated. Although its appearance closely resembles that of real needles, the needle tip is blunt. Furthermore, the Streitberger needle features a special handle that enables the blunt needle to press against the skin surface and retract into the handle rather than penetrate the skin. Nonetheless, a pricking sensation similar to that of actual needle insertion will be generated in the skin at the acupoint during this process. Comprehensive details regarding the verum/sham acupuncture method and needle sizes can be found in Figure 3.

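### The patient information stated in section 2.5 presents both needle types and both tablets as theoretically able to improve PDS, but the plan itself describes one of each as a placebo

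*Protocol article*

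**What the plan says.** Section 2.5 (Blinding) sets out what patients hear: "Patients will be informed that the study involves two types of acupuncture treatment and two types of drug, which theoretically can improve PDS symptoms". The next sentence adds that everyone, whatever the group, gets one type of acupuncture combined with one type of drug.

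Other parts of the article describe the same components differently:

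- Section 2.6.1, in the text after Table 1, on the second needle: "The Streitberger needle is a non-penetrating acupuncture placebo device that has been well validated".
- Section 2.5, on the second tablet: "Itopride placebo tablets will be indistinguishable from verum itopride tablets in taste and appearance". Section 2.6.2 also calls it a placebo.
- Section 2.6, on the third arm: "Patients in the sham acupuncture plus placebo group will take itopride placebo tablets for 20 days and receive 12 sessions of sham acupuncture treatment".

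Section 2.2 describes the information given before consent in general terms: "Participants interested in this trial will be informed about the purpose and process of the study as well as potential risks and benefits". The consent form itself is not shown.

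Two further statements bear on the consequences. The responder outcome in section 2.7.1 is self-rated: "Participants will be requested to evaluate changes in their symptom relief over the preceding 7 days via a 7-point Likert scale". The Introduction criticises earlier unblinded trials for "potentially allowing patient preferences for acupuncture to influence clinical outcomes".

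**The concern.** On its ordinary reading, the clause about theoretical benefit covers all four components. If it is read as covering only the drugs, it still presents the placebo tablet as able to improve PDS. Nowhere does the plan attribute a therapeutic effect to the blunt needle or to the placebo tablet. This is a positive statement that the plan contradicts, so it is not a complaint about missing detail.

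Two things are at stake.

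- **Information for the decision to join.** Receiving other FD treatment during the study is an exit criterion (section 2.3.4). The chance of receiving no active therapy therefore matters to a prospective participant.
- **Interpretation.** The sham-plus-placebo arm is the trial's only internal check that either active treatment works in these patients. With a self-rated outcome, telling patients that everything they might receive can help may raise response in that arm and narrow its distance from the others.

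**Working it through.** **Step 1. Who receives what.** Inputs: 201 participants (section 2.11) and allocation to the three groups, ending with the "sham acupuncture plus placebo group in a 1:1:1 ratio" (section 2.4). Each arm has 201 / 3 = 67.

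| Arm | Needle | Tablet | Inert components | n |
|---|---|---|---|---|
| Verum acupuncture plus placebo | verum | placebo | 1 | 67 |
| Itopride plus sham acupuncture | sham | itopride | 1 | 67 |
| Sham acupuncture plus placebo | sham | placebo | 2 | 67 |

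- Sham needle: 67 + 67 = 134 of 201.
- Placebo tablet: 67 + 67 = 134 of 201.
- At least one inert component: 201 of 201.
- Only inert components: 67 / 201 = 33.3%.

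The misdescription reaches everyone. The third arm is where it matters most.

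**Step 2. The plan's own sample size.** Inputs from section 2.11: 70.69% acupuncture, 55.46% itopride, margin −10%, one-sided 0.025, power 80%. With unpooled variance:

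n = [p₁(1−p₁) + p₂(1−p₂)] × (1.960 + 0.842)² / (p₁ − p₂ + 0.10)²

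= (0.2072 + 0.2470) × 7.849 / 0.2523² = 56.01, rounded up to 57 per group, as stated. Then 57 / 0.85 = 67.06, stated as 67, and 3 × 67 = 201. The calculation uses no response rate for sham plus placebo, and the article gives none.

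**Step 3. How sensitive the sham contrast is (illustration only).** The sham-plus-placebo rate is an assumption and is varied over a range. Power uses 57 per arm, two-sided 0.05, normal approximation with pooled variance under the null:

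power = Φ{ [ |p₁ − p₀| − 1.960 √(2p̄(1−p̄)/57) ] / √([p₁(1−p₁) + p₀(1−p₀)]/57) }, where p̄ = (p₁ + p₀)/2.

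| Assumed sham-plus-placebo rate | Verum (70.69%) vs sham plus placebo | Itopride (55.46%) vs sham plus placebo |
|---|---|---|
| 30% | >99% | 79% |
| 40% | 92% | 38% |
| 45% | 80% | 20% |
| 50% | 62% | 8% |

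The active rates are held fixed here, so the table shows what happens if response rises in the sham-plus-placebo arm alone. An equal rise in percentage points in all arms would leave the differences as they were. The table shows that the contrast is sensitive to that rate. It does not show that the wording moves it.

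**Step 4. Direction for non-inferiority.** With 57 per arm and unpooled variance, power = Φ[(p₁ − p₂ + 0.10)/SE − 1.960].

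| Acupuncture | Itopride | Power |
|---|---|---|
| 70.69% | 55.46% | 81% |
| 70.69% | 60% | 65% |
| 70.69% | 70.69% | 22% |
| 63% | 63% | 20% |

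Under the plan's assumed advantage of 70.69 − 55.46 = 15.23 points, narrowing the difference makes non-inferiority harder to show.

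**The case against.** The strongest reply is that one sentence in the Blinding section of a condensed article is not the whole patient information. The consent form is not shown and may disclose the sham and the placebo, and section 2.2 does not exclude this. That stands, so no conclusion can be drawn about what patients actually sign. It does not remove the point: if the form does disclose placebo, section 2.5 conflicts with the form as well as with sections 2.6 to 2.6.2.

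The wording is also hedged. It speaks of theoretical improvement, and nothing says that patients are told there is no placebo. That is fair, but the hedge still attributes possible benefit to components that the plan calls placebo.

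A reader might infer several stronger things that the documents do not support:

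- **That placebo response is raised, by a known amount.** Nothing in the documents shows or sizes a rise. It is a plausible inference from a self-rated outcome and the plan's own remark about patient preference.
- **That one arm is favoured.** All arms hear the same sentence, and each active arm has exactly one active and one inert component. Nothing shows an unequal effect on the acupuncture-itopride comparison.
- **That non-inferiority becomes easier to reach.** Narrowing would have that effect only if acupuncture were truly worse than itopride. Under the planned rates it works the other way (Step 4).
- **That nothing in the trial bears on expectation.** The Expectation for Treatment Scale is collected at week 1 (section 2.7.2). It concerns acupuncture only and cannot isolate the effect of this sentence, but it does measure the proposed mechanism.

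One practical objection also stands. Telling patients that one needle does not penetrate would name the feature that separates the arms and could threaten the blind. The correction has to avoid that.

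**Conclusion.** The point holds as an internal contradiction: section 2.5 states patient information that the plan's own description of the needles and tablets does not support. It touches all 201 participants, each of whom receives at least one inert component. It weighs most on the 67 (33%) who receive only inert components. This part rests on the text and the allocation ratio alone.

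The consequence for the results is a possibility and not a demonstrated bias. It rests on the assumption that the message lifts self-rated response more where no active treatment is given than in the active arms. If so, the contrast with sham plus placebo weakens, and with it the evidence that either active treatment works. The documents give neither a sham-plus-placebo rate nor any measure of the lift, so no size can be stated. The sentence should be corrected, but it does not invalidate the design.

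**What to change.** In section 2.5, delete the closing clause that attributes theoretical benefit to the treatments. State instead that patients will be told that:

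- a sham needle and a placebo tablet are used;
- one in three participants will receive neither active treatment;
- neither they nor the observers will know which combination they receive.

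Do not describe the physical feature that distinguishes the needles. Align the consent form and the staff script with this text.

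The patient blind does not depend on the deleted clause. It rests on the matched tablet, the Streitberger needle and treatment in separate rooms, and all of these remain.

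The cost is an amendment approved by the ethics committee, which section 2.10 already requires for any protocol change. Possibly a few more people will decline, and response may be somewhat lower in all arms.
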